#### Recruitment {15}

Patient recruitment will take place in several centres in Belgium: Universitair Ziekenhuis Brussel, AZ Turnhout, AZ Delta, AZ Sint-Maarten and Jessa Ziekenhuis. Patients were recruited from January 14, 2022, onwards. Depending on the rate of inclusion, we will contact other centres as well. Recruitment is expected to last for 2 years with an estimated rate of recruitment of 1 to 2 patients per month in each centre. Treating neurosurgeons or anaesthesiologists (regional coordinating investigator or his/her designee) will inform eligible patients about the project when patients are eligible for a treatment trajectory with subthreshold SCS.

### Assignment of interventions: allocation

#### Sequence generation {16a}

Patients will be randomly allocated (1:1 ratio) to BMT or subthreshold SCS using a computer-generated random list (Sealed Envelope Ltd., available from: https://www.sealedenvelope.com/simple-randomiser/v1/lists [Accessed 28 Dec. 2021]). To reduce predictability of a random sequence, a blocking procedure will be used including random block sizes of 2 and 4 patients. Randomisation will be stratified by investigational site.

#### Concealment mechanism {16b}

Only an unblinded researcher will have direct access to the randomisation list (Excel-file, which will be inaccessible for the outcome assessor and statistician).

#### Implementation {16c}

The unblinded researcher will generate the allocation sequence and is responsible for informing the patients and physicians to which group the patients are randomised.

### Assignment of interventions: blinding

#### Who will be blinded {17a}

Due to the nature of the treatments, the treating physicians and patients could not be blinded to the treatment group. The statistician and outcome assessor will be blinded to group allocation. With regard to this, patients will be asked not to communicate with the assessors about the intervention received.

#### Procedure for unblinding if needed {17b}

The statistician and outcome assessors will be remained blinded during the trial.

### Data collection and management

#### Plans for assessment and collection of outcomes {18a}

At baseline, all outcome measurements will be evaluated except for the impression of change and healthcare expenditure. For both groups, follow-up assessments will take place after 1 month, 6 months (primary endpoint) and 12 months. All outcome measurements will be collected through an online platform (Qualtrics), except for healthcare expenditure that is collected through a diary (up to 6 months) and at 12 months with a questionnaire. At 1 month and 12 months, outcome measurements can be completed without an additional hospital visit. Patients will receive a link towards the questionnaires to complete them online. In case patients do not have access to online resources, patients can fill in the questionnaires at the hospital, where the outcome assessor will be blinded to group allocation. With regard to this, patients will be asked not to communicate with the assessor about the intervention they received. At the 6-month follow-up, patients will complete the questionnaires at the hospital, whereafter they may cross-over towards the other intervention group in shared decision with the treating physician.

#### Plans to promote participant retention and complete follow-up {18b}

Patients receive a reminder of upcoming appointments and follow-up phone calls to promote participant retention and completion. For two follow-up visits, data will be collected remotely to minimise the burden for patients.

#### Data management {19}

Data will be collected via web-based self-reported questionnaires. To avoid missing data, an error will appear in case a question is not filled in. Collected data will include answers to validated questionnaires related to the patients’ overall pain intensity, disability, medication use, health-related quality of life, global impression of change, work status, competencies for self-management, healthcare expenditure, anxiety and depression. In addition, patients will be asked about the number of previous spine surgeries and general demographic data. Written informed consent of the patients will be collected and provides the basis for the legal ground for the data management.

During the research, the unblinded researcher is responsible for data management and storage. Following the research, the PI will be fully responsible for data management and storage. During the research, all obtained data will be stored on a dedicated page on Vrije Universiteit Brussel SharePoint (system-encrypted) with access limited to the TRADITION researchers. A back-up will be foreseen on a secure external hard drive. Following the research, all data will be relocated to the Vrije Universiteit Brussel Archive where it will be archived for 25 years. All possible personal identifiable data (vide infra) will be removed from the archived data.

Personal data will be processed in accordance with the ongoing European Union’s Data Protection Directive and regulation, the relevant Belgian legislation concerning data protection of July 30, 2018, and good clinical practice. As we collect personal identifiable data, following steps are taken to limit unauthorised access. Informed consents will be preserved at a secure location at the Vrije Universiteit Brussel. Qualtrics (Qualtrics, Provo, UT) will be used for data collection to improve data protection as responses to questionnaires will only be accessible to the investigator. Collected data will be password protected. Personal identifiable and clinical trial data will be separated, with the latter receiving a unique participant ID. Access to informed consents, personal identifiable data and the link with the participant ID will be restricted to the researchers and stored separately from the trial data. Eventual further dissemination of data will only occur in a pseudonymised or aggregated way.

The Vrije Universiteit Brussel supports the FOSB metadata standard (= dataset metadata schema defined by the Flemish Open Science Board) which can be mapped to the international DataCite metadata schema. At the project level, the general information (title, investigators, aim, objectives, concepts, hypotheses, funder), protocol, sampling procedure, instruments, hardware and software used to collect data, data handling log, accessibility of the data and data manipulations will be provided in research plans and publications. At the database level, an inventory of the files will be provided in a read-me file. At the data level, a codebook will be provided on how to handle quantitative variables together with the scripts to analyse the data.

#### Confidentiality {27}

Participant identification codes will be used to link data to patients. The file containing the linking between participant numbers and personal data (i.e. key) will be managed by the researchers and will be locked for access by others. As an additional security measure, the file linking the pseudonymisation to the original direct identifiers will be encrypted before it is uploaded to SharePoint.

#### Plans for collection, laboratory evaluation and storage of biological specimens for genetic or molecular analysis in this trial/future use {33}

No biological specimens will be obtained during the conduct of the trial.

### Statistical methods

#### Statistical methods for primary and secondary outcomes {20a}

Considering the longitudinal data, a generalised estimating equation will be constructed to evaluate and compare therapy effects. The primary outcome will be analysed as the proportion of clinical holistic responders from baseline to 6 months (taking into account the longitudinal nature of the trial) between both groups. Baseline variables will be used as covariates. For secondary outcome measurements, a similar strategy will be applied with longitudinal mixed models. This longitudinal data analysis approach will also be applied for 12 months data. Statistical as well as clinical significant differences will be defined at alpha < 0.05. Furthermore, based on the baseline data, we will determine predictive factors and which subgroup of patients will benefit the most of the treatment. All analysis will be performed in SAS or R.

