### Objectives {7}

Given the substantial socioeconomic impact of SCS implantations, given that currently no direct high-quality evidence is available for subthreshold SCS versus BMT and given the lack of a holistic outcome to guide the treatment choice between subthreshold SCS versus BMT in patients with PSPS-T2, we here propose a randomised controlled trial to answer this question.

The primary scientific objective is to examine whether subthreshold SCS, compared to BMT, provided to patients with PSPS-T2 results in a different proportion of clinical holistic responders at 6 months. The secondary objective of the study is to examine if subthreshold SCS compared with BMT is different in improving patients’ individual competencies for self-management, increasing the likelihood to return to work, work status and healthcare expenditure, improving pain relief, obtaining pain medication reduction, decreasing anxiety and depression, increasing quality of life and decreasing disability.

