### Outcomes {12}

#### Primary outcome

The primary outcome measure is the proportion of clinical holistic responders at 6 months. This outcome measure consists of a combination of 5 questionnaires whereby all criteria need to be fulfilled to be considered a clinical holistic responder. For questionnaires where a minimal clinical important difference (MCID) is available, patients should reach this cut-off value. A patient is considered a responder if all of the following criteria are fulfilled:

30% VAS pain intensity reduction for overall pain compared to baseline [29]41% reduction in pain medication use compared to baseline [30]30% improvement on Oswestry disability index (ODI) compared to baseline [29]MCID on EuroQol (EQ-5D)-5L compared to baseline [31]Minimally improved, much improved or very much improved on Patient Global Impression of Change (PGIC) [32]

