At baseline, all outcome measurements will be evaluated except for the impression of change and healthcare expenditure. Follow-up assessments will be performed one month after the start of the individualized best conservative treatment (BMT group) or 1 month after IPG implantation (SCS group), 6 months after start of the intervention (intermediate effects and primary endpoint) and 12 months (long-term effects) after intervention initiation. At 1 month and 12 months, outcome measurements can be completed without an additional hospital visit. Patients will receive a link towards the questionnaires to complete them online. At the 6-month follow-up, patients will complete the questionnaires at the hospital. After filling in the questionnaires at the 6-month follow-up visit, patients could change treatment groups (in both directions). This decision will be a shared decision between the patient and treating physician in case the randomised intervention did not provided enough pain relief. The cross-over will be mainly performed from BMT towards subthreshold SCS, according to study results obtained by Kumar et al. who evaluated standard SCS compared to BMT [10]. Figure 1 presents the project flowchart.

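### The primary GEE is worded as running from baseline, where responder status is undefined, and does not name the 6-month contrast as the primary test

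*Protocol article*

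**What the plan says.** The endpoint is tied to one time point. Under Primary outcome: "The primary outcome measure is the proportion of clinical holistic responders at 6 months". Objectives {7} asks whether subthreshold SCS, against BMT, "results in a different proportion of clinical holistic responders at 6 months". The rule is strict: "all criteria need to be fulfilled to be considered a clinical holistic responder". Four of the five criteria (pain, medication, ODI, EQ-5D-5L) are judged against the baseline value. The fifth is the PGIC. On timing, the outcomes section states: "At baseline, all outcome measurements will be evaluated except for the impression of change and healthcare expenditure". Plans for assessment and collection of outcomes {18a} repeats this. Follow-up is at 1, 6 and 12 months.

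The analysis is in Statistical methods {20a}: "a generalised estimating equation will be constructed to evaluate and compare therapy effects". It continues: "The primary outcome will be analysed as the proportion of clinical holistic responders from baseline to 6 months", with a parenthesis that the longitudinal nature of the trial is taken into account. Then: "Baseline variables will be used as covariates". The longitudinal approach is extended to the 12-month data. The paragraph does not say which visits form the response or which contrast decides the primary question.

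Under Sequence generation {16a}: "Randomisation will be stratified by investigational site". Site is not named in the analysis paragraph.

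**The concern.** The analysis sentence departs from the endpoint in two ways. It starts the response series at a visit where the outcome cannot be observed, and it spans a period where the endpoint names a single visit. Both bear on what the primary test measures.

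A gap between the 1- and 6-month effects is plausible in this design. Under the intervention description, the pulse generator follows only a trial period with at least 50% reduction in both pain and medication, which exceeds the 30% and 41% responder cut-offs. The 1-month visit is counted from generator implantation in the SCS group but from the start of treatment in the BMT group. Implanted patients therefore reach that visit recently selected on two of the five components. A treatment effect averaged over visits would carry this into the primary result. If the model form stays open, it could also be settled only after a first version fails to fit.

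**Working it through.** The protocol gives no numerical result for the GEE, so there is no figure of its own to reproduce here. The check has two parts: whether the outcome exists at baseline, and what each reading of the sentence would estimate.

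**Inputs.** From Sample size {14}: 47.8% responders on SCS, 12.6% on BMT, 57 per arm. Assumed, because the document gives none: the 1-month responder rates, a latent within-patient correlation of 0.5, and equal 6-month rates of 30% in the no-effect scenario.

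**1. Baseline value.** Four criteria compare a later score with baseline, so they have no content at baseline itself. The PGIC is not recorded then. All five are required, so the composite is undefined. It can only be set to 0 for everyone by construction.

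**2. The target.** The 6-month difference is 47.8% − 12.6% = 35.2 points. On the logit scale: ln(0.478/0.522) − ln(0.126/0.874) = −0.088 + 1.937 = 1.849.

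**3. Baseline rows coded 0, categorical time.** In one simulated trial (57 per arm), 22/57 SCS and 5/57 BMT patients were responders at 6 months. The raw log odds ratio is ln(22/35) − ln(5/52) = −0.464 + 2.342 = 1.878. The binomial-logit GEE with group-by-visit terms put the baseline log-odds at −26.57. Standard errors ran from about 304 to 1,195, with one undefined, although the software reported convergence. The group-by-6-month change from baseline had an estimate of 1.88 and a standard error of 677. The 6-month point contrast from the same fit was 0.00 + 1.88 = 1.88, which agrees with the raw value.

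**4. Baseline rows coded 0, linear time.** With 47.8% vs 12.6% at both visits and a large sample, six times the group-by-time slope was 0.408 against the target 1.849. In repeated simulations the group-by-time test rejected in 11% to 13% of runs, against 94% to 99% for the 6-month contrast (45 evaluable per arm where stated).

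**5. One effect common to the 1- and 6-month visits.** Large-sample log odds ratios, with BMT at 12.6% at 1 month:
- 1-month SCS rate 20%, 6-month rates as planned: 1.33 (target 1.85).
- 1-month SCS rate 60%, 6-month rates as planned: 2.11 (target 1.85).
- 47.8% vs 12.6% at 1 month, 30% in both arms at 6 months: 0.85, an odds ratio of about 2.3 (target 0).

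With a larger 1-month gap (47.8% vs 5%) and 30% in both arms at 6 months, the common-effect test rejected in 80% to 86% of runs. The 6-month contrast rejected in about 3% to 6%.

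**6. Post-baseline visits, treatment-by-visit, 6-month contrast.** In the simulated trial: 1.811 + 0.067 = 1.878, equal to the raw value. In large samples it gave 1.85 to 1.86 in the three scenarios with the planned 6-month effect, and −0.01 in the one without.

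**7. Site.** Five sites of about 23, 80% followed, 2,000 runs, unadjusted z test against Cochran-Mantel-Haenszel, assumed between-site logit SD of 1.0:
- Type I error 3.3% vs 4.5%.
- Power 83.3% vs 86.5% (42% vs 12.6% responders).
- Power 64.0% vs 68.0% (35% vs 12.6% responders).

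At an SD of 0.5 or below, ignoring site cost nothing.

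**The case against.** The strongest reply is that the phrase is loose, not wrong. Response from baseline to 6 months can mean response judged over that interval. The next sentence gives baseline variables the role of covariates, and nowhere is baseline called an outcome row. An undefined outcome would normally drop out of a GEE, leaving the 1- and 6-month visits. The endpoint is named as 6 months throughout the article. Link, working correlation and time coding are usual content of an analysis plan that is not shown. The simulated figures rest on assumed 1-month rates and on model forms that the article does not state.

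Much of this stands. A reader might infer that the planned GEE must either fail to fit or test the wrong quantity. The document does not support that: step 6 is a permissible reading and on target, and step 3 shows that the 6-month point contrast stays finite even with baseline zeros. Nor are the rejection rates in steps 4 and 5 properties of this plan. They show what certain readings would do.

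What does not stand is that the benign readings settle the matter. A single change-derived value per patient has no longitudinal structure, yet the paragraph opens with longitudinal data, repeats the point in the parenthesis and extends the approach to 12 months. The reading with 1- and 6-month visits meets the endpoint only if the 6-month contrast is the primary test, and the paragraph does not say so. An analysis plan would have to depart from the sentence as written, not merely add detail to it.

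**Conclusion.** The point holds as a defect in the stated primary analysis. The wording begins at a visit where the outcome is undefined under the protocol's own definition, and covers a period where the endpoint is one visit. Taken literally, with baseline as a repeated response, the baseline cell is degenerate and the group-by-time change from baseline is not estimable. A visit-common treatment effect would estimate a 1- and 6-month average. Under the assumed 1-month rates it ranges from 1.33 to 2.11 against a target of 1.85, and reaches 0.85 where there is no 6-month difference. The undefined baseline status follows from the document alone; the sizes depend on the assumed rates and correlation.

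This does not show that the trial cannot answer its question, since a valid analysis lies within the wording. The site point is minor: the gain is 3 to 4 points of power at an assumed logit SD of 1.0 and none at 0.5 or below.

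**What to change.** Reword the primary-analysis sentences in Statistical methods {20a} to this effect:

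> The GEE response is responder status at the 1- and 6-month visits only. Baseline values enter only as covariates. The model contains treatment, visit, treatment-by-visit and site (small sites pooled if needed). The primary test is the treatment contrast at 6 months.

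If the 12-month data are modelled the same way, the response should again be post-baseline visits only. A cap on the number of baseline covariates and a standardised risk difference as the reported measure are optional.

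The cost is a wording change to the protocol and any analysis plan, made before the data are analysed. No new data or visits are needed.

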### Trial design {8}

TRADITION is a two-arm, cross-over multicentre randomised controlled trial to evaluate whether subthreshold SCS results in more clinical holistic responders in PSPS-T2 patients compared with BMT. This research is a post-market clinical follow-up (PMCF) investigation [25]. Patients will be randomised (1:1) to (a) BMT or (b) subthreshold SCS. After the assessment at 6 months, patients are allowed to switch groups in case of unsatisfactory responses. Patients will have a follow-up period until 12 months after the start of the intervention.

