#### Methods in analysis to handle protocol non-adherence and any statistical methods to handle missing data {20c}

Both intention-to-treat as well as per protocol analyses will be conducted to determine whether both definitions of the population will point towards similar results, which could improve robustness of the results. At first, analysis will be performed on data as observed. Hence, intermittent missing is not expected to substantially bias the results. To address possible informative drop-outs, a sensitivity analysis will be performed using multiple imputation, including all available information on background characteristics and outcome. All analysis will be performed in SAS or R.

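### After response-driven switching at 6 months, the 12-month between-group models compare starting strategies, not long-term subthreshold SCS versus BMT

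*Protocol article*

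**What the plan says.** Statistical methods {20a} plans a generalised estimating equation for the primary outcome and mixed models for the secondary outcomes, to compare therapy effects between the groups. For the primary outcome: "The primary outcome will be analysed as the proportion of clinical holistic responders from baseline to 6 months". The section then adds: "This longitudinal data analysis approach will also be applied for 12 months data". It mentions no switching term and does not say what the 12-month contrast estimates.

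Trial design {8} states: "After the assessment at 6 months, patients are allowed to switch groups in case of unsatisfactory responses". The last paragraph under Secondary outcomes, in Outcomes {12}, allows the change in both directions once the 6-month questionnaires are complete, "in case the randomised intervention did not provided enough pain relief". It also gives the expected direction: "The cross-over will be mainly performed from BMT towards subthreshold SCS". The same paragraph describes the 12-month assessment as showing long-term effects. Concomitant care {11d} asks BMT patients to hold off SCS for the first 6 months only.

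On populations, section {20c} says: "Both intention-to-treat as well as per protocol analyses will be conducted". It treats similar results from the two as a sign of robustness. It does not define the per-protocol set and does not mention the switch. Its multiple imputation addresses drop-out.

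**The concern.** The protocol predicts that treatment will change between 6 and 12 months, mostly in one direction and because of the patient's own result. It then carries the 6-month comparison of therapies across that change. By 12 months many patients in the randomised BMT arm may have received SCS.

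Two misreadings become likely. A small 12-month difference could be taken as loss of SCS efficacy when it reflects BMT patients receiving SCS. A difference that remains could be taken as the effect of sustained SCS over sustained BMT, which it does not measure. Objectives {7} ties only the primary objective to 6 months. The secondary objective has no time limit, so readers may naturally take the 12-month results as answering it.

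**Working it through.** The protocol gives no 12-month figure to reproduce. The only planning figures are the 6-month responder proportions in Sample size {14}, taken here as stated: pS = 47.8% for SCS and pB = 12.6% for BMT. The planned difference is 47.8 − 12.6 = 35.2 points.

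**Assumptions, none from the protocol:**
- A share c of BMT non-responders switches to SCS, and BMT responders stay.
- Nobody switches from SCS to BMT.
- Without a switch, 6-month status persists.
- Switchers respond at rate r. The upper value is r = 47.8%. The lower value allows for the 12% trial failure rate in {14}: r = 0.88 × 47.8% = 42.1%.

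**1. Contrast by randomised arm.** BMT arm at 12 months = pB + (1 − pB) × c × r, with 1 − pB = 0.874.

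| c | share of BMT arm switching | r | BMT arm at 12 months | SCS minus BMT |
|---|---|---|---|---|
| 50% | 43.7% | 47.8% | 0.126 + 0.874 × 0.5 × 0.478 = 33.5% | 14.3 points |
| 50% | 43.7% | 42.1% | 0.126 + 0.874 × 0.5 × 0.421 = 31.0% | 16.8 points |
| 70% | 61.2% | 47.8% | 0.126 + 0.874 × 0.7 × 0.478 = 41.8% | 6.0 points |
| 70% | 61.2% | 42.1% | 0.126 + 0.874 × 0.7 × 0.421 = 38.3% | 9.5 points |

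The SCS arm is held at 47.8% throughout. If the 12% discount applied to that arm too, the no-switch difference would itself be 42.1 − 12.6 = 29.5 points, and the contrast would shrink from there to 42.1 − 31.0 = 11.1 or 42.1 − 38.3 = 3.8 points.

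**2. Switching unrelated to response.** If a share s of the whole BMT arm switches at random and then responds at 47.8%, the difference is (1 − s) × 35.2. That gives 26.4, 17.6 and 8.8 points for s = 25%, 50% and 75%. Dilution therefore does not depend on switching being tied to non-response.

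**3. A per-protocol set that drops switchers, if that is how it is defined.** Responders among remaining BMT patients = pB / (pB + (1 − pB)(1 − c)).
- c = 50%: 0.126 / (0.126 + 0.437) = 22.4%, a difference of 25.4 points.
- c = 70%: 0.126 / (0.126 + 0.262) = 32.5%, a difference of 15.3 points.

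The BMT rate rises from 12.6% with no patient's outcome changed. The rise is selection alone.

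**4. What is not touched.** The 6-month questionnaires are completed before any switch (Outcomes {12}; Plans for assessment {18a}), and the within-trial economic evaluation in {20b} stops at 6 months.

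**The case against.** The strongest reply is that nothing is wrong with the 12-month model itself. Analysis by randomised arm keeps the protection of randomisation and answers a real question about which treatment to start with. This stands. A reader might infer that the 12-month intention-to-treat analysis is invalid, and the documents do not support that. The fault is in what the contrast is taken to mean. It is also fair that {20a} carries over an approach without spelling out the 12-month contrast. Comparison by randomised group is the natural reading, since that is what the approach does at 6 months.

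A reader might also infer that the protocol plans a per-protocol analysis restricted to satisfied BMT patients and will cite its agreement with intention-to-treat at 12 months. The text does not say this. Switching after 6 months is permitted, so a switcher need not be a protocol deviator. The set's definition may properly sit in an analysis plan that is not shown, and the robustness remark in {20c} names no time point. The per-protocol point is therefore conditional.

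The figures are open to challenge too. No switch rate is given. The protocol ties switching to insufficient pain relief or response, not to failing the five-part composite, so some composite non-responders may stay. Switchers need a trial period first and would have less than 6 months on SCS at the 12-month visit. These objections limit the precision of the illustration but do not remove the dilution.

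**Conclusion.** The point holds in this form. Applied as written, the 12-month analysis by randomised arm estimates SCS first versus BMT with optional SCS from 6 months. It does not estimate the long-term effect of SCS versus BMT, and nothing else in the protocol article corrects that reading. If SCS works and switching is mainly from BMT to SCS, the contrast is expected to move toward zero.

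The size cannot be derived from the documents. With 50% or 70% of BMT non-responders switching and a 42% to 48% response after the switch, 35 points become roughly 14 to 17 or 6 to 10. A reader might push the switch rate higher and infer a reversal in favour of BMT. At c = 90% the difference is −2.4 points with r = 47.8% but +2.1 with r = 42.1%, so the sign rests on the assumption and carries no weight.

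If switchers are excluded at 12 months, the remaining BMT patients are selected on response, and agreement with intention-to-treat would not show robustness. The 6-month primary and secondary comparisons and the within-trial economic evaluation stand as planned.

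**What to change.** In {20a}, confine the SCS-versus-BMT efficacy claim to data up to 6 months. Keep the 12-month analysis by randomised arm, but label it as early SCS versus BMT with optional SCS after 6 months. Report the number of switches in each direction by arm, and show switchers' outcomes descriptively.

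In {20c}, state that any 12-month analysis excluding switchers is non-randomised and will not serve as evidence of robustness. Align the description of the 12-month assessment in Outcomes {12} with the new label. If an effect without switching is wanted, define it separately, with a method for response-dependent switching and its assumptions.

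The cost is wording in the protocol and analysis plan. Recruitment, treatment, visits and sample size do not change. The sponsor forgoes a 12-month SCS-versus-BMT claim that the design cannot support.

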#### Sample size {14}

Sample size calculation was performed using the formula for large sample tests for proportions [50] and more specifically to test for equality between the proportion of clinical holistic responders in both interventions. The estimated proportion of clinical holistic responders is estimated at 47.8% in the subthreshold SCS group [51] and assumed to be 12.6% in the BMT group. The latter is an assumption based on the mean of the difference in primary outcome measures from the PROCESS and PROMISE trials at 6 months since no values for clinical holistic responders in BMT are available yet [10, 11]. By assuming an equal allocation, a sample size of 114 participants is needed with 57 participants in each intervention group. This sample size calculation accounts for a 20% loss to follow-up after 6 months and a 12% trial failure rate [51]. Calculations were performed for achieving an 80% power at the 5% level of significance.

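### The protocol defines clinical significance by the same p-value threshold as statistical significance, which mainly affects the labelling of secondary and 12-month results

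*Protocol article*

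**What the plan says.** The statistical methods section {20a} describes a generalised estimating equation for the primary outcome. On the other outcomes it says: "For secondary outcome measurements, a similar strategy will be applied with longitudinal mixed models". It extends the longitudinal approach to the 12-month data and then adds: "Statistical as well as clinical significant differences will be defined at alpha < 0.05". Because of where it stands, the sentence covers the primary, secondary and 12-month comparisons.

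The Primary outcome section uses thresholds of size, but for single patients. It says "For questionnaires where a minimal clinical important difference (MCID) is available, patients should reach this cut-off value" and lists 30% for VAS pain, 41% for medication, 30% for the ODI, the MCID for the EQ-5D-5L and at least minimal improvement on the PGIC. All five must be met for a patient to count as a responder.

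No section says how large a difference between the arms would be clinically important, either for the responder proportion or for any secondary outcome.

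**The concern.** Statistical significance says whether the data are compatible with no difference. Clinical significance says whether the difference is large enough to matter. One p-value threshold cannot do both jobs, because the same observed difference falls on either side of 0.05 depending on how many patients were evaluable and how variable the scores were.

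The rule can mislabel in two directions. A modest difference that just reaches p < 0.05 is called clinically significant, although its confidence interval reaches almost to zero. A larger difference that is estimated less precisely is called not clinically significant. The second risk is real here because the trial was sized on the responder proportion and not on the secondary outcomes.

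About ten secondary measures are exposed: VAS, medication score, ODI, EQ-5D-5L, PGIC, work status, PAM, HADS anxiety, HADS depression and healthcare expenditure. The dissemination plan takes the findings to stakeholders and patient organisations, who would naturally read the label as a statement about benefit to patients.

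**Working it through.** The fault lies in a definition, so there is no plan figure to correct. The arithmetic shows where the rule would put the line.

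**Inputs**
- Sample size {14}: "a sample size of 114 participants is needed with 57 participants in each intervention group".
- Sample size {14}: "This sample size calculation accounts for a 20% loss to follow-up after 6 months and a 12% trial failure rate". Applying both losses gives 57 × 0.80 × 0.88 = 40.1, so about 40 evaluable per arm. The range used is 57 (no loss) to 40.
- Sample size {14}: "Calculations were performed for achieving an 80% power at the 5% level of significance". Sidedness is not stated. Two-sided is assumed because the calculation is described as a test of equality.
- Sample size {14}: responder rates of 47.8% (SCS) and 12.6% (BMT), a planned difference of 47.8 − 12.6 = 35.2 points.
- VAS SD: not in the article. A range of 15 to 25 mm is assumed.

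**The plan's own figure.** The usual two-sided pooled formula for 47.8% against 12.6% at 80% power gives [1.96 × √(2 × 0.302 × 0.698) + 0.8416 × √(0.478 × 0.522 + 0.126 × 0.874)]² / 0.352² = 25.5, so 26 per arm. After both losses this is 26 / 0.704 = 37, or 26 / 0.68 = 39 if the losses are added. The stated 57 is not reproduced. That is a separate matter: 57 is the planned number and is taken as given here.

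**Continuous outcomes.** The smallest standardised difference that reaches two-sided p < 0.05, unadjusted and at one time point, is 1.96 × √(2/n).

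| Evaluable per arm | Threshold | SD 15 mm | SD 20 mm | SD 25 mm |
|---|---|---|---|---|
| 57 | 0.367 SD | 5.5 mm | 7.3 mm | 9.2 mm |
| 40 | 0.438 SD | 6.6 mm | 8.8 mm | 11.0 mm |

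The same 7 mm difference is therefore clinically significant under the rule with 57 per arm and SD 15 mm (threshold 5.5 mm), and not clinically significant with 40 per arm and SD 25 mm (threshold 11.0 mm). Nothing about its meaning to patients has changed.

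**Responder proportion.** Take BMT near 12.6% and a pooled z test.
- 57 per arm: 16/57 against 7/57 is 28.1% − 12.3% = 15.8 points, p = 0.036. With Fisher's exact test, 17/57 is needed (17.5 points).
- 40 per arm: 13/40 against 5/40 is 32.5% − 12.5% = 20.0 points, p = 0.032. With Fisher's exact test, 14/40 is needed (22.5 points).
- 40 per arm, one responder fewer: 12/40 against 5/40 is 17.5 points. The pooled rate is 17/80 = 0.2125, the standard error is √(2 × 0.2125 × 0.7875 / 40) = 0.0915, z = 0.175 / 0.0915 = 1.91, and p = 0.056.

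So 15.8 points earns the label at 57 per arm and 17.5 points does not at 40 per arm. The label follows precision and not size.

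**The case against.** Five objections deserve an answer.

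- **Conflict with the responder cut-offs.** A reader might infer that the sentence contradicts the Primary outcome section. It does not. Those cut-offs classify one patient's change from baseline, whereas the sentence concerns differences between groups. The objection stands: the fault is in the sentence itself.
- **Any difference, however small, would qualify.** A reader might infer this too. At this sample size it is not so: the threshold is about 0.37 to 0.44 SD, or about 16 to 20 responder points. For the primary outcome, a patient counts only after meeting all five criteria, so a significant difference is already a difference in patients with meaningful change. This also stands, and it confines the harm mainly to the secondary and 12-month results.
- **The illustration does not prove that 5.5 to 11 mm is trivial.** Correct. The article gives neither a VAS SD nor a between-group margin. The planned analysis is a longitudinal mixed model, so its threshold will differ from the unadjusted one. A confidence limit near zero is also true of any result that just reaches p < 0.05. The figures show that the label moves with precision, and no more.
- **The sentence may only be loosely worded.** It could mean that score differences and the responder comparison are both tested at 0.05. That is possible, but it is not what the sentence says, and nothing else in the article says so.
- **This belongs to the SAP.** An unstated margin could be left there. A stated rule that is wrong is a different matter.

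**Conclusion.** The point holds in limited form. Section {20a} states a rule that uses a p-value to decide clinical significance, and no other section sets a between-group criterion that overrides it. Followed as written, secondary and 12-month differences would be labelled clinically significant or not by p-value alone. The line would fall at about 0.37 to 0.44 SD for 57 to 40 evaluable per arm, or about 5.5 to 11 mm on the VAS. This assumes a two-sided unadjusted comparison at one time point and a VAS SD of 15 to 25 mm. With fewer evaluable patients at 12 months, the threshold would be higher.

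The hypothesis tests, models, populations and sample size do not change, and neither does the primary conclusion on statistical significance. What changes is the label on the results, in both directions.

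**What to change.** Remove the reference to clinical significance from the sentence in section {20a}, so that two-sided p < 0.05 defines statistical significance only. Then add a sentence to this effect: clinical relevance is judged separately, from the estimated between-group difference and its 95% confidence interval. For outcomes with a cut-off in the responder definition, it is also judged from the between-group difference in the proportion of patients reaching that cut-off, with its 95% confidence interval.

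A between-group mean difference should not be compared directly with a within-patient MCID. The two are on different levels, and the article supplies the MCID only as a rule for individual change.

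The change needs no new data, no further patients and no new primary test, and it should be made before the analysis. Its downside is that fewer outcomes can be called clinically significant.
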